### Statistical methods

#### Sample size

The required number of subjects has been determined to be 82, from preliminary data in literature: to our knowledge the sole RCT about rehabilitation in subacute/chronic stages of PFP (participants enrolled from 9 months into the onset of paresis) using SFGS included 50 participants, among whom only 24 benefited from rehabilitation (waiting list without any rehabilitation in the other group) [62].

In contrast with that trial, participants of the control group of the present study will benefit from an intervention (physiotherapy and/or speech therapy), which will be associated with the potential to improve clinical status. We thus hypothesize that there will be a minor improvement of + 10 points in the Sunnybrook composite score in that group. Based on that hypothesis and to demonstrate an improvement of + 20 points (with a standard deviation up to 13) for the experimental group, considering a 5% alpha risk (bilateral test) and a statistical power of 90%, we will include 41 patients per group for 36 analyzed (assuming a 10% loss of follow-up).

Regarding the secondary objectives, it should be noted that this sample size will be comparable to other reliability and validity studies for the FaCE scale (*n* = 67 to 122 patients; [47, 48, 59–61] and larger than the initial Sunnybrook validation study (*n* = 19; 12). Regarding reliability parameters such as the intraclass correlation coefficients (ICC) and for ICC values expected to be > 70%, the suggested sample size will allow estimating ICCs with an accuracy of ± 15% for two measures and ± 10% for three measures and more [63]. Strategies for achieving adequate participant accrual to reach the target sample size will involve communication on the study with ENT specialists, speech therapists and physiotherapists in the greater Paris area.

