#### Statistical analysis

Descriptive statistical analysis will be carried out to evaluate randomization groups in terms of demographic, and initial clinical and kinematic characteristics, including PFP cause, delay since injury, side of paresis, previous drug treatments, and comorbidities. Quantitative data will be described using means (± SD) or medians (with IQR), depending on the normality of distributions, and qualitative data will be reported as numbers or percentages.

Changes in the Sunnybrook Composite score between D1 and D180 will be evaluated by Student’s *t* test. No interim analysis has been planned. The primary outcome analysis will be performed using Intention to treat (ITT) analysis. Comparative analysis of quantitative values at J90 and J180 – including primary and secondary outcomes—will be performed with Student’s *t* tests for independent samples or with Mann–Whitney non-parametric tests, depending on conditions. Changes in quantitative values from inclusion to each assessment visit (D90-D1, D180-D1) will be compared taking into account the baseline data in case of baseline intergroup differences despite randomization. Within-group changes will be tested through Student’s *t*-tests for matched data or Wilcoxon Rank sum tests, depending on the conditions. Multiple linear regression models will be tested to identify independent predictors associated with the changes in quantitative parameters over time, including longitudinal analysis of random effects (mixed models).

Comparative analysis of binary parameters will be run through Chi-square or Fisher’s exact tests, depending on conditions. Multivariable analysis will be generated through logistic regression models. Intra- and inter-rater reliability studies will use frequencies of agreement, intraclass correlation coefficients, Cohen and Fleiss kappa coefficients and coefficients of variation. Spearman or Pearson coefficients will be calculated between scores on the various scales, depending on conditions. Complementary analyses on the primary outcome and all analyses regarding secondary outcomes will be performed in both ITT and per protocol (PP) populations to describe the excluded patients of the PP population and to evaluate the robustness of the results.

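### The non-parametric option for within-group changes is the Wilcoxon rank-sum test, which ignores the pairing of visits; it should be the signed-rank test

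*Protocol article*

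**What the plan says.** All the relevant text is in the Statistical analysis section of the protocol article.

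- Within-group changes: "Within-group changes will be tested through" Student's t tests "for matched data or Wilcoxon Rank sum tests, depending on the conditions". The t test is the first option and is the paired version. The alternative is the rank-sum test.
- Between-group comparisons at the follow-up visits: Student's t "tests for independent samples or with Mann–Whitney non-parametric tests, depending on conditions".
- Primary outcome: "Changes in the Sunnybrook Composite score between D1 and D180 will be evaluated by" Student's t test.
- Visits that define a change: "Changes in quantitative values from inclusion to each assessment visit (D90-D1, D180-D1").

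The Wilcoxon signed-rank test is not named anywhere in the article.

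**The concern.** A within-group change compares the same patients at two visits, so the data come in pairs. The rank-sum test pools the two sets of scores and ranks them as though they came from different people, discarding the information on who is who. The paired rank test is the signed-rank test. As written, the section uses one independent-samples procedure, under two names, for both independent and paired data.

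The alternative could well come into use. The section makes the choice depend on conditions that it does not define, and several outcomes are ordinal. The Background describes the Sunnybrook scale as ordinal with few grades, and Outcome measures gives ordinal scoring for the SF-12 and FACE-Q. At stake is the reporting of change within an arm: a real but modest change could be missed.

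**Working it through.** **Inputs from the Sample size section.** There are 36 analysed patients per group. The control arm is expected to show a "minor improvement of + 10 points in the Sunnybrook composite score in that group", and the target is an "improvement of + 20 points (with a standard deviation up to 13) for the experimental group". Testing is two-sided at 5% with 90% power.

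**Inputs the article does not give (assumptions).** These are the correlation ρ between D1 and follow-up; whether 13 is the SD of change or the SD at one visit; and the 5-point change, included to show a modest effect.

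**The plan's own figure.** For the between-group difference of 20 − 10 = 10 points:

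n per arm = 2 × (1.960 + 1.282)² × 13² / 10² = 35.5, so 36.

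Allowing for 10% loss, 36 / 0.9 = 40, and the plan enrols 41. Power with 36 per arm is 0.904 by the normal approximation and 0.896 by the exact t calculation. The stated size is reproduced. It concerns the between-group test; the article states no power for within-group tests.

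**Why the level falls.** With SD σ at each visit, the variance of the mean change is 2σ²(1 − ρ)/n. An independent-samples test assumes 2σ²/n. Its statistic under no change therefore has SD √(1 − ρ) instead of 1, and its true level is roughly 2Φ(−1.96/√(1 − ρ)):

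- ρ = 0.5: 1.96/0.707 = 2.77, level about 0.006
- ρ = 0.7: 1.96/0.548 = 3.58, level about 0.0003
- ρ = 0.8: 1.96/0.447 = 4.38, level about 0.00001

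**Simulation.** 4,000 samples of 36 bivariate normal pairs, two-sided 5%. Entries are rejection rates.

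Reading (a): 13 is the SD of change, so the SD at each visit is 13/√(2(1 − ρ)).

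| ρ | No change, rank-sum | +5 rank-sum | +5 signed-rank | +10 rank-sum | +10 signed-rank | +20 rank-sum |
|---|---|---|---|---|---|---|
| 0 | 0.049 | 0.603 | 0.596 | 0.992 | 0.991 | 1.000 |
| 0.3 | 0.022 | 0.446 | 0.607 | 0.976 | 0.990 | 1.000 |
| 0.5 | 0.006 | 0.297 | 0.585 | 0.945 | 0.992 | 1.000 |
| 0.7 | 0.001 | 0.106 | 0.594 | 0.796 | 0.993 | 1.000 |
| 0.8 | 0.000 | 0.026 | 0.596 | 0.535 | 0.994 | 1.000 |
| 0.9 | 0.000 | 0.001 | 0.607 | 0.098 | 0.991 | 0.986 |

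The signed-rank test holds its level (0.046 to 0.051 under no change) and has power 1.000 at +20 throughout.

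Reading (b): 13 is the SD at each visit, so the SD of change is 13√(2(1 − ρ)).

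| ρ | +5 rank-sum | +5 signed-rank | +10 rank-sum | +10 signed-rank |
|---|---|---|---|---|
| 0 | 0.359 | 0.356 | 0.876 | 0.870 |
| 0.3 | 0.316 | 0.444 | 0.917 | 0.959 |
| 0.5 | 0.292 | 0.602 | 0.941 | 0.991 |
| 0.7 | 0.262 | 0.817 | 0.977 | 1.000 |
| 0.8 | 0.232 | 0.938 | 0.989 | 1.000 |
| 0.9 | 0.195 | 0.999 | 0.999 | 1.000 |

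At +20 both tests reach 1.000. At +10 the largest loss is 0.991 − 0.941 = 0.05.

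**The case against.** The strongest reply is that this is a slip of the pen. The sentence concerns within-group changes and sets the Wilcoxon test beside a matched t test, while the same section calls the independent-samples test Mann–Whitney. The authors very probably meant the paired Wilcoxon test, and a competent analyst might run it without comment. That is likely, but the text still names the wrong test. In Stata, which the article specifies, the two tests are separate commands, and a silent correction would depart from the published plan.

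A reader might infer more: that within-group changes as a whole will be tested wrongly and with badly reduced power. The article does not support that.

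- The paired t test is the first option; only the alternative is wrong.
- At the article's own +20 points there is no material loss. At +10 the loss is severe only if 13 is the SD of change and the correlation is about 0.7 or more. The starkest figures come from a 5-point change that the article never mentions.
- The simulated pairs are normal, the case in which the t test would probably be chosen. The figures show what ignoring the pairing costs; they do not forecast results on skewed or ordinal data.

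A reader might also infer that the assessment of the Créteil Scale's responsiveness is compromised. Outcome measures says only that responsiveness will be explored and does not tie it to this test.

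**Conclusion.** The non-parametric alternative for within-group changes is wrong as written, and nothing else in the article corrects it. If used literally, it is invalidly conservative whenever visits are positively correlated. It can hide modest within-arm changes but does not raise the risk of a false claim of improvement.

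The size of the power loss rests on an unstated correlation and on which SD the figure of 13 denotes. It ranges from negligible (+20 on either reading; +10 with a cross-sectional SD) to large (+5, or +10 with SD of change 13 and high correlation). Some positive correlation is plausible, since Table 1 requires chronic and stable paresis, but its value is not given.

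The affected analyses are secondary. The primary between-group t test, the between-group Mann–Whitney option and the sample size do not depend on this sentence. Severity is minor.

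**What to change.** In the within-group sentence of the Statistical analysis section, replace the Wilcoxon rank-sum test with the Wilcoxon signed-rank test, and use Stata's signrank command instead of ranksum for these comparisons. Leave Mann–Whitney in place for the between-arm comparisons. The cost is one phrase in the protocol, carried into the analysis plan and program. Sample size, visits, data collection and the primary analysis do not change.

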**Exclusion criteria:**
- Evolving tumor causing the peripheral facial paresis
- Facial botulinum toxin injection less than six months before enrollment in the study, or planned during the study period
- Facial surgery less than two years before enrollment into the study or planned during the study period
- V-VII or XII-VII anastomosis or muscle transfer prior to enrollment into the study or planned during the study
- Nonsurgical aesthetic treatments – hyaluronic acid / lipofilling / laser / tensor thread – less than two years before enrollment in the study or planned during the study period
- Recurrent facial paresis
- Participation in another interventional research protocol on the face (aesthetic, rehabilitative, or surgical)
- Intercurrent disorder that could hinder the ability to participate in the rehabilitation program
- Preexisting cognitive, mental or psychological disorder preventing participation in the rehabilitation program or in the follow-up assessments, based on the opinion of the investigator
- Patient under legal protection

Randomization will be performed on inclusion day (D-30) by the chief investigator of each center, between the Conventional therapy group (CONV) and the Guided Self-rehabilitation Contract (GSC) group (see Randomization procedure below). Each participant will thus be randomly assigned to one of the two arms and will receive a rehabilitation program depending on the randomized arm, to be carried out over six months. In order to minimize any nocebo effect for the conventional treatment group, the study coordinator will not disclose details of the Guided Self-rehabilitation Contract to the physicians and physiotherapists who treat participants in the CONV group, nor to the CONV participants themselves.

Facial rehabilitation will begin the day after the first evaluation (D1).

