### Data management

All information required by the protocol will be entered in the eCRF. Data will be collected as they are obtained. Any missing data will be coded. Every site will have access to the eCRF via a web-based data collection system. Investigators will be given a document offering guidance on using this tool. Each investigator will be responsible for the accuracy, quality and relevance of all the data entered. An audit trail of all changes will be saved. The computer file used for this research is implemented in accordance with French (amended “Informatique et Libertés” law governing data protection) and European (General Data Protection Regulation – GDPR) regulations. The sponsor has obtained the authorization of the CNIL (“*Commission Nationale de l’Informatique et des Libertés*”, French Data Protection Agency) before implementing any of the data processing required to conduct the research. If a subject stops participating or withdraws consent, the data collected up to the date of cessation will be analyzed. If a subject is lost to follow-up, the investigator should make every effort to reconnect with the patient. Subjects who have prematurely stopped their participation in the research will not be replaced.

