All missing or invalid data will be systematically sought for verification in patient charts. In addition to the analysis performed on complete cases without missing data for the primary outcome, sensitivity analysis will be performed using various methods of replacement of missing data, including the LOCF method (Last Observation Carry Forward), the worst-case assumption, and multiple account assignment by chained equations (MICE). Participants who terminate the study prematurely will not be replaced. All analyzes will be performed with Stata software v14.1 (StataCorp, College Station, TX, USA).

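### The primary analysis is labelled intention-to-treat, but its estimate comes from complete cases only; the multiple imputation that would keep all randomised patients is a sensitivity analysis

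*Protocol article*

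**What the plan says.** All references are to the protocol article.

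- **Label.** Statistical analysis: "The primary outcome analysis will be performed using Intention to treat (ITT) analysis".
- **Variable and test.** The same section: "Changes in the Sunnybrook Composite score between D1 and D180 will be evaluated by" Student's t test. A patient needs both a D1 and a D180 score to contribute.
- **Missing data.** The last part of that section: "In addition to the analysis performed on complete cases without missing data for the primary outcome, sensitivity analysis will be performed". The replacement methods named are LOCF, worst case and multiple imputation by chained equations (MICE). Patients who stop early are not replaced.
- **Expected numbers.** Sample size: 41 per group included, 36 per group analysed, with a stated 10% loss.
- **Timing.** Procedures: "Randomization will be performed on inclusion day (D-30) by the chief investigator of each center". Participants are then told their arm. D1 comes about a month later.
- **Scores collected.** Table 2 has the Sunnybrook scale at D-30, D1, D90 and D180.
- **Patients who stop.** Data management: "the data collected up to the date of cessation will be analyzed".

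**The concern.** An intention-to-treat label tells the reader that every randomised patient is compared in the arm assigned. The estimate that will carry the label leaves out anyone without a D1 or a D180 score, including patients lost in the month between randomisation and D1. The plan expects this: its own sample size sets 36 analysed against 41 randomised.

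A comparison of completers is safe when loss is unrelated to outcome, or related to it in the same way in both arms. Here the arms differ in burden. GSC asks for daily series to fatigue on three muscle groups plus a diary for six months, while in CONV the therapist sets frequency and content. Participants know their arm. Loss that depends on response differently by arm is therefore plausible, and it would bias the primary estimate. The data and methods to reduce that risk are already in the plan, but they do not supply the primary result.

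**Working it through.** **1. Inputs from the Sample size section.** Control: "a minor improvement of + 10 points in the Sunnybrook composite score in that group". Experimental: "to demonstrate an improvement of + 20 points (with a standard deviation up to 13) for the experimental group". The difference is 20 - 10 = 10 and the SD is 13; alpha is 0.05 two-sided and power 90%.

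**2. The plan's own figure.** n per arm = 2 × (1.960 + 1.282)² × 13² / 10² = 35.5, so 36, as stated. Inflating for 10% loss gives 36 / 0.90 = 40, against 41 stated, which is close enough. Going from 41 to 36 is a loss of 5/41 = 12.2% per arm, or 10 of 82 overall. The stated plan therefore implies 10-12% loss from the primary analysis.

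**3. Illustration of bias.** The documents give no dropout by arm, so the following are assumptions:
- GSC loses patients at random from the lower half of D90 response.
- CONV loses patients at random.
- The D90-D180 correlation of change is 0.7, and the SD is 13 at both visits.

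The lower half of a normal distribution averages 0.798 SD below the mean. Carried to D180, the dropouts average 0.7 × 0.798 × 13 = 7.26 points below their arm. If a fraction f is lost, completers average f/(1 - f) × 7.26 above the arm mean:

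| Loss in GSC | Bias | Complete-case estimate (true 10) |
|---|---|---|
| 10% | 0.111 × 7.26 = +0.8 | 10.8 |
| 5 of 41 (12%) | 5/36 × 7.26 = +1.0 | 11.0 |
| 20% (twice the stated loss) | 0.25 × 7.26 = +1.8 | 11.8 |

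Simulation of 41 per arm agrees (10.8, 11.0, 11.8). Assuming also mean D90 changes of 5 (CONV) and 10 (GSC), LOCF gave 9.2, 9.0 and 8.4. A regression using D90 gave 10.0 throughout, which is expected because dropout was made to depend on D90 alone.

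**4. Same dropout in both arms.** If both arms lose patients from the lower half of D90 response, the two shifts cancel. Simulation gave 9.95, 9.93 and 10.0 at 10%, 12% and 20% loss. If only CONV loses its poor responders, the sign reverses: about -0.8 to -1.0 at 10-12%.

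**5. Scale.** The standard error of the difference is 13 × √(2/36) = 3.06, so a bias of 1.0 is about one third of a standard error. With no true effect, type I error under step 3 is about 6%.

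**6. Wider range.** With 5 of 41 lost per arm, CONV at random, and an assumed correlation between final outcome and GSC dropout:

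| Correlation | Bias | Type I error |
|---|---|---|
| 0 | about 0 | 5% |
| 0.3 | +0.9 | 6% |
| 0.5 | +1.5 | 8% |
| 1 (the five worst GSC responders) | +2.9 | 19% |

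The last row is an extreme bound.

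**The case against.** Three missing-data analyses are prespecified for the primary outcome, and one of them, MICE, is a method proposed here as primary. Worst case is itself a stress test. The label can also be read as analysis by assigned arm, in contrast to per-protocol: a GSC patient who does not exercise but attends D180 stays in GSC. Participants are selected for motivation, telephoned four times and pursued if lost.

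Much of this stands, and it limits the point. It does not change which result is primary: a complete-case estimate under an intention-to-treat label.

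Three stronger readings are tempting, and the documents do not support them.

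- **That the GSC effect will be inflated.** No dropout by arm and no reasons for leaving are given. Unimproved CONV patients might leave instead, which would push the estimate the other way.
- **That dropouts' scores are ignored.** LOCF and MICE can use them, and the Statistical analysis section also plans D90 comparisons and mixed models without calling them sensitivity analyses. The scores are missing only from the primary estimate.
- **That the plan contradicts its promise to analyse data up to cessation.** The Data management section does not say in which analysis, and the planned secondary and sensitivity analyses can meet it.

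Nor are LOCF and worst case errors in the plan, since neither is the primary estimate. Dropping LOCF would be a preference.

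**Conclusion.** The point holds as a mismatch between label and method, with a conditional and modest consequence. The complete-case choice is stated, and the 36 of 41 analysed confirms it, so this is not a detail left to a later document.

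Any bias requires dropout to relate to outcome differently by arm, which is plausible but undocumented. Under the one-sided illustration it is about +0.8 to +1.0 points on a 10-point effect at 10-12% loss. It is about zero if loss is random or alike in both arms, and negative if CONV loses its poor responders. These sizes rest on the assumed correlation of 0.7 and the lower-half rule, neither of which is in the documents. The issue matters more if loss exceeds the plan, is concentrated in one arm, or the true effect is small.

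**What to change.** State that the primary analysis includes all randomised participants by arm, with the D180 contrast primary, using one of:

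- the MICE analysis already planned, imputing from arm and the D-30, D1 and D90 scores; or
- a mixed model for repeated measures that includes the D-30 score as one of the repeated measurements.

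The D-30 score is essential: a model on D1, D90 and D180 alone would still drop patients lost between randomisation and D1. Move the complete-case t test to sensitivity. Optionally, add a delta-adjusted imputation beside the planned worst case, to cover loss that depends on unobserved values.

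The cost is a wording change and slightly more analysis work. The primary result would then rest on a missing-at-random assumption, which should be stated. No extra visits are needed because Table 2 already collects the scores, and no extra patients because 36 per arm already gives 90.4% power by the normal approximation. Trial status reports 33 of 82 included in December 2022; the change should be made before the database is frozen and before any comparison by arm is seen.

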### Safety

Assistance Publique—Hôpitaux de Paris (APHP), sponsor of this research, has contracted an insurance for the duration of the study, in compliance with the law on biomedical research, guaranteeing its own civil liability, as well as that of any investigator or staff involved in conducting the research.

## Discussion

To our knowledge, this study will be the first controlled study evaluating a facial motor strengthening program, through the strategy of Guided Self-rehabilitation Contracts, in the challenging treatment of chronic facial paresis. The study also represents uncommon involvement of a neurorehabilitation team, classically involved with central motor disorders, into the field of peripheral facial paresis. There are a number of arguments that support the plausibility that motor strengthening might help patients: (i) recover better emotional facial animation and (ii) reduce facial muscle overactivity.

